## Abstract

**Background:**

Most children do not consume the recommended amount of fruit and vegetable (FV) servings. Changing the school food environment can be a cost-efficient, effective approach to improving children’s dietary quality. There is great popular support for school salad bars as a means to increase children’s FV intake within the National School Lunch Program (NSLP), yet empirical research is limited. Further, although FV consumption can facilitate healthy weight management if these foods replace high calorie items, there is a need to enhance understanding of salad bars’ influence on children’s diet quality and energy intake within the NSLP. This is particularly important to investigate in schools in communities characterized by high poverty, as students they serve are particularly likely to rely on school meals.

**Methods:**

This report describes the design and rationale of a federally-funded investigation that uses validated methods to evaluate school salad bars. This district plans to install salad bars into 141 elementary schools over 5-years, facilitating the conduct of a waitlist control, cluster randomized controlled trial. Specifically, 12 pairs of matched schools will be randomly selected: half receiving a salad bar (Intervention) and half serving pre-portioned FVs only, standard under the NSLP (Control). Thus, groups will have different FV presentation methods; however, all schools will operate under a policy requiring students to take at least one FV serving. Schools will be matched on Title I status and percent of racial/ethnic minoritized students. Intake will be objectively assessed at lunch in each school pair, prior to (baseline), and 4–6 weeks after salad bars are installed (post), yielding ~ 14,160 lunch observations throughout the study duration. Cafeteria sales and NSLP participation data will be obtained to determine how salad bars impact revenues. Finally, implementation factors and cafeteria personnel’s perspectives will be assessed, to identify barriers and facilitators to salad bars use and inform sustainability efforts. Proposed methods and current status of this investigation due to COVID-19 are described.

**Discussion:**

Results will have great potential to inform school nutrition policies and programs designed to improve dietary quality and reduce obesity.

**Trial registration:**

Retrospectively registered (10/28/22) in clinicaltrials.gov (NCT05605483).

## Background

Fruits and vegetables (FVs) are essential components of a healthy diet and can reduce risk for many chronic illnesses; [1, 2] yet, most children do not consume the recommended number of servings of these foods [3–5]. This is concerning, as inadequate FV intake is linked to increased risk for cardiovascular disease, [1, 2] and certain cancers [6]. Children from minoritized backgrounds living in communities characterized by high poverty have the lowest FVs intake [7]. These children often live in food deserts with limited FV affordability and access [8, 9]. They are also the most likely to participate in the National School Lunch Program (NSLP), [10] making the school food environment a critical target of public health efforts to enhance dietary quality [11, 12].

A major goal of the NSLP is to increase FV intake, with a long-term aim of reducing obesity, [12] yet it is unclear how increasing children’s FV intake relates to energy intake in the NSLP [13]. Greater FV consumption could decrease energy intake if these foods replace higher-calorie items; however it could increase energy intake if FVs are merely added to regular meals [13–16]. Understanding how FV consumption influences energy intake in school lunch is particularly important to examine in schools serving predominantly minoritized children living in communities characterized by high poverty, as this population faces disproportionately high obesity risk [17] and is most likely to be impacted by school food policies, given its reliance on the NSLP [10].

Salad bars are promoted as a strategy to increase students’ FV intake, variety, and choice within the NSLP [18–22]. For example, the Chef Ann Foundation raised >$15.8 million and donated 6,083 salad bars to schools, with 260 schools on a waiting list to receive one [23]. The Centers for Disease Control (CDC) notes that it supports the mission of *Salad Bars to Schools* (a public-private partnership which includes the Chef Ann Foundation, the Whole Kids Foundation, and government programs) as a strategy, “to ensure every child has the choice of healthy fruits and vegetables each day at school.” [23]. Yet, rigorous evaluation of school salad bars to determine their impact on dietary intake patterns is needed to ensure they meet their intended purpose.

Increasing accessibility to a variety of FVs and fostering choice are two mechanisms proposed to explain how salad bars might positively impact dietary consumption [19–22, 24–27]. However, the limited research investigating this relation has yielded somewhat mixed results. For example, results of one study indicated that greater variety of FVs offered (independent of salad bar status) was associated with higher FV intake among elementary school students [22]. Similarly, the introduction of salad bars into Title I schools was associated with increases in the variety of FVs offered and selected [28]. Yet, self-served *portions were smaller* and FV intake *decreased* [28].

Fostering choice might be an especially helpful in promoting FV intake in children. Indeed, in one study conducted with 4th and 5th grade students (*N* = 1193), 85% reported that they liked having the option to choose FVs from their school salad bar; however only 44% said they used the salad bar at least once per week [28]. A limitation of that investigation was that salad bars were offered *in addition* to fixed portions of FVs on the lunch line, increasing variety, yet precluding isolation of presentation methods; this design also introduced confounds related to FV familiarity (e.g., of canned [29] and/or heated FVs) competing with salad bars.

In addition to fostering choice, scholars have posited that salad bars might impact dietary consumption by increasing FV intake, and decreasing overall caloric consumption, via energy displacement [30]. Yet it is unclear how increasing FV intake affects children’s overall energy consumption, in part due to methodological limitations of extant research. [16, 31, 32]. Even less is known about how increasing FV intake within the NSLP (which limits calories available per meal) influences energy intake at lunch. One of the few existing studies in this area found that increased lunch FV intake was associated with decreased self-reported energy intake in students at schools with salad bars [33]. In contrast, a subsequent study [16] found that students who consumed the most FVs at lunch had the highest total energy intake. However, non-FV energy decreased across FV intake groups (thus at least some energy consumed from other sources was displaced by FVs). This study was conducted prior to the current NSLP guidelines, and only 54% of the schools it evaluated had salad bars. In a cross-sectional investigation conducted under the current NSLP, students in schools with salad bars consumed more energy from vegetables compared with students from schools without salad bars. Yet, evidence was inconsistent regarding FV displacement of other lunch calories [34].

Other limitations of previous research include a lack of longitudinal and objective data [35]. For example, in multiple cross-sectional studies, middle and high school students self-reported greater FV intake in schools with salad bars [36–38]. However, because dietary intake was assessed via self-report only it is more subject to bias than objectively measured consumption. In contrast, 1st -5th grade students’ FV intake (assessed via objective plate waste) was no higher in schools with salad bars compared with schools serving pre-portioned FV only [22]. However, this latter work was conducted > 15 years ago and might not be generalizable to today’s children, particularly given significant changes to the NSLP. There are also several program evaluations available online, although methodological concerns limit their internal validity (e.g., lack of comparison groups, post-only assessments, or low validity of FV assessment methods) [35].

Only two quasi-experimental studies [28, 33] have prospectively examined the impact of salad bars on dietary intake among elementary school students, and they yielded conflicting results. Moreover, only one of these investigations, [28] was implemented under the current NSLP standards and assessed dietary intake objectively. In the first of these studies, Slusser et al. [33] compared FV intake before and after salad bar installation in three schools. FV intake increased by 1.12 servings per day, as measured by 24-hour recalls; however, objective assessments of FV consumption were not conducted. There was also a 2-year gap between baseline and post assessments (and a 30% student transience rate), introducing potential history effects and reducing the likelihood that the same children were assessed at both time points. Bean and colleagues recently assessed FV intake before and one month after salad bars were installed in two Title I elementary schools serving predominately Black children, all of whom received free meals [39]. Using objective, digital imagery plate waste methods, they found that students selected significantly more *types* of FVs after the introduction of salad bars. However, at post, self-served FV portions were significantly smaller than those served by food service personnel, and mean FV intake *decreased* by 0.65 cups (c), compared to when FVs were pre-portioned exclusively [28]. These results suggest that increasing access to FVs might not be sufficient on its own to shape consumption patterns in this population. Importantly, neither of these prior studies included comparison groups.

Bean and colleagues subsequently compared FV intake in schools with salad bars with matched schools serving proportioned FVs only, within this same district. Although there was some evidence that vegetable consumption was higher in salad bar schools, different patterns of FV selection and consumption were observed across school pairs, suggesting that school environment factors other than salad bar access influenced FV intake [40]. Importantly, salad bars in this district were offered *in addition to* pre-portioned FVs on the serving line, and salad bar usage varied widely (8–64%) between schools. The continued availability of pre-portioned FVs precluded the ability to isolate the effects of salad bars on dietary consumption. There were also between-school differences in salad bar location, a factor demonstrated to impact usage [41]. These results highlight the need for rigorously-designed, prospective evaluations of school salad bars, that include larger numbers of schools and comparison groups, use robust scientific methods, assess dietary intake objectively, and place salad bars in a consistent location.

Finally, salad bars are also often proposed as a mechanism to enhance NSLP participation [35]. NSLP participation is a priority across districts, as it enhances the economic stability of school nutrition departments [42]. Greater NSLP participation could also have positive public health implications, as school meals offer superior nutrition, compared with meals brought from home [42]. Despite these benefits of NSLP participation, it has consistently declined over time [43]. Moreover, there are no empirical data to support the claim that salad bars increase participation in the NSLP. The current study will examine how salad bars impact cafeteria sales and NSLP participation within a diverse district, with wide variations in NSLP participation, enhancing generalizability of findings related to these critical revenue sources.

In sum, there is an urgent need to improve the quality of children’s dietary intake. Optimizing school meals within the NSLP can have a significant public health impact. Tremendous resources have been invested in school salad bars as a means to increase FV intake, yet it is not known if they achieve this goal. By randomly selecting schools receiving salad bars, matching them with those serving pre-portioned FV only, and conducting a comprehensive, longitudinal evaluation that includes objective, validated assessments of dietary intake, this investigation will address these critical gaps. Specifically, this study will identify: (1) how salad bars impact dietary consumption in NSLP lunches, and (2) consequences of, and barriers and facilitators associated with, salad bar implementation. It will also examine the potential moderating role of the school-level sociodemographic factors of percent high obesity risk racial/ethnic minority students and Title I status on dietary consumption, and salad bar implementation barriers and facilitators. In the current study, all FVs on the salad bars will be fresh and *replace* all fixed portion FVs on the serving line. All schools will operate under a policy requiring students to take at least one FV serving [44]. This will allow examination of the independent and combined impact of variety and choice, two mechanisms with potential to increase FV intake, within the NSLP. We hypothesize that schools with salad bars will manifest greater increases in both FV selection and consumption, and decreases in FV waste, compared with schools without salad bars. In addition, we hypothesize that schools with salad bars will have greater improvements in dietary quality and reductions in total energy intake at lunch, compared with schools without salad bars.

Data from this trial will yield some of the clearest evidence related to salad bars to date, providing a strong evidence base to evaluate school nutrition policies designed to enhance dietary intake and reduce health disparities within the NSLP. Results can guide resource allocation and inform targeted interventions and policies designed to reduce obesity.

## Methods and design

### Study setting

This study will be conducted in a large public school district in the Mid-Atlantic United States. This district plans to install salad bars in all 141 elementary schools (K-6th grades). Prior to the onset of the current trial, 50 salad bars had already been installed. There are thus 91 schools remaining for potential inclusion in the proposed investigation, with salad bars to be installed over a 3-year period. Salad bars are launched throughout the year. This installation schedule provides a unique opportunity to evaluate a natural experiment, with a waitlist control design. Specifically, randomly selected schools receiving salad bars will serve as Intervention schools and be matched with Control schools serving pre-portioned FVs only. These waitlist (Control) schools will receive salad bars in the subsequent school year. Thus, this investigation offers a unique and *time-sensitive* opportunity to conduct a waitlist control, cluster randomized controlled trial.

### Design

Twelve pairs of matched schools will be randomly selected: half will receive a salad bar (Intervention; replacing all other FVs) and half will only serve pre-portioned FVs, standard under the NSLP (Control). Thus, groups will have different FV presentation methods; however all schools will be operating under a policy requiring students to take at least one FV serving [44]. In contrast to prior salad bar research, [28] salad bars in the current study will replace all other FVs on the lunch line, and students can select their entire meal from the salad bar. This implementation model facilitates a more rigorous comparison between schools with and without salad bars than that conducted in prior research. Schools will be matched on Title I status (a proxy for socioeconomic status [SES]) and percent of racial/ethnic minority students based on higher obesity risk. Dietary intake at lunch will be objectively assessed in each pair of schools, prior to (baseline), and 4–6 weeks after salad bars are installed (post), resulting in ~ 14,160 lunch observations throughout the study duration. The primary dependent variable of interest is change in FV intake, assessed using digital imagery plate waste methods. Cafeteria sales and NSLP participation data will also be examined to assess the potential impact of salad bars on these critical revenue sources. Finally, we will assess implementation practices and cafeteria personnel’s perspectives, to identify barriers and facilitators to salad bars and inform sustainability efforts.

Prior to random selection, each school will be assigned to one of 4 categories based on sociodemographic variables. We used information from schools that received salad bars in the first 2 years of the district’s program (prior to the current study) to develop matching procedures. Matching was based on: 1) Title I status, which includes % free and reduced-price lunch, and 2) % of students from racial/ethnic backgrounds at higher risk of obesity (Native American, African American/Black, Latinx, Native Hawaiian/Pacific Islander, more than one race). Four categories of schools resulted: A = < 40% minoritized AND not Title I; B = 40–60% minoritized AND not Title I; C = 40–60% minoritized AND Title I; and D = > 60% minoritized AND Title I. Matching procedures were then applied to the remaining 91 schools, demonstrating that each category has adequate numbers of schools in each year of this study to successfully execute the proposed aims.

As illustrated in Fig. 1 and 16 different schools will be included (A1➔D4), 4 from each sociodemographic category. In Year 1, 8 schools will be randomly selected: 4 with salad bars (A1➔D1; Intervention), matched with 4 serving pre-portioned FVs only (A2➔D2; Control). In Year 2, these 4 control schools will receive salad bars and become Intervention schools, and will be matched with 4 new, randomly selected Control schools (A3➔D3). These procedures will be repeated in Year 3, with A3➔D3 becoming Intervention schools, matched with new randomly selected Control schools (A4➔D4). There will ultimately be 12 pairs of matched schools (12 Intervention [shaded green in Fig. 1] and 12 Control [shaded yellow]).

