**Fig. 1 Fig1:**
[figure not shown]
Design of wait-list control randomized controlled trial of school salad bars

Each pair of Intervention and Control schools will be assessed concurrently, minimizing the threats maturation and history effects pose to internal validity [45]. Baseline and post-assessments within each pair will be conducted on days with the same menu cycle whenever possible, which controls for potential confounds, such as the varying palatability of meals and seasonal variations in food availability (the district’s schools have 5 week menu cycles). We will also control for month of assessment in all analyses. This is particularly important in the elementary school setting, where students are continually adjusting to the environment and school breaks can affect eating habits [46]. Inclusion of baseline assessments will allow us to control for any baseline differences between schools. Raters will be masked to avoid potential bias. Moreover, conducting independent double ratings of ~ 20% of meals will further minimize the influence of any potential bias. Finally, this study’s internal validity is enhanced by matching schools on key variables prior to randomization, so that they differ primarily on presence of a salad bar [45]. Matching procedures were carefully developed to evaluate how school-level factors of race/ethnicity and SES might moderate the impact of salad bars. Other variables that could potentially vary between schools and impact outcomes will be carefully monitored and considered in analyses (e.g., NSLP participation or school environment factors). Plate waste assessments will be conducted in wait list control schools during two consecutive years; however, students will not know the purpose of the assessments, and their prior experience with these (minimally obtrusive) methods is not likely to alter dietary behaviors during the following school year.

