## Statistical analyses

### Power analysis

Power and effect size of the multilevel models that will be used to analyze the variety of outcomes in our cluster RCT are a function of a number of parameters: (1) the number of clusters (J = 16 independent schools [8 Intervention and 8 Control]), (2) the cluster size (*n* = 295 lunches per school), and (3) the ICC (estimated as 0.01, 0.05, and a much more conservative 0.10), which takes into account the correlated nature of our data and is the ratio of variability between clusters to the total variability [66]. Optimal Design Plus Empirical Evidence v3.01 software [67] was used to calculate the minimum detectable effect size given the parameters above, α = 0.05, and a desired power of 80%. For ICCs of 0.01, 0.05, and 0.10, we have 80% power to detect small to medium effect sizes of 0.17, 0.35, and 0.48, respectively. Thus, our proposed sample of 14,160 observations will be more than adequate to evaluate the study aims.

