### Analyses

Prior to analyses, distributions of all measures will be examined. Contingency tables and frequency distributions will be evaluated (for categorical and continuous variables, respectively), and transformations considered. Outliers will be checked for errors before being used in analyses. Sex differences will be assessed for all outcomes; if significant differences are found, analyses outlined below will be stratified by sex. All tests will be 2-sided at α = 0.05 level, corrected for multiple comparisons, and conducted in SAS v9.3.

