Analyses are dictated by the cluster RCT study design. Data are hierarchical, gathered in multiple levels. The first level of measurement is from students, clustered within schools, the second level of measurement. We are measuring consumption based on students, yet their treatment assignment is defined by the school’s assignment. This nested structure must be considered in analyses as the assignment of intervention to the schools can result in students within schools being positively correlated for the outcomes. Without accounting for correlated nature of the data, Type 1 error rate for the intervention effect might be inflated and the significance of the study findings misinterpreted. Multilevel Linear Modeling (MLM) is a type of regression used to analyze nested data as it can accommodate fixed and random effects and correlated observations within units of assignment (schools). SAS PROC MIXED (for continuous variables) and PROC GLIMMIX (for dichotomous and polytomous data) have MLM applications which take into account random effects and correlated observations and will be used in these analyses. Potential covariates include grade, NSLP participation, and month of assessment, and factors related to the school cafeteria environment that might differ between schools (e.g., lunch duration), where appropriate. Using these models, we will evaluate differences between Intervention and Controls schools in types and variety of FVs and categories of vegetables selected, and subsequent consumption (% consumed/wasted) at baseline and 4–6 weeks after salad bars are installed. Variety will be recorded as the number of different types of FVs selected for each meal, and the number of categories of vegetables (ranging from 1 to 5; corresponding with USDA categorization) [44]. For the primary outcome (FV consumption), plate waste ratings will be calculated for fruits, vegetables, each specific FV category, and also averaged across FVs. We will also evaluate the effect of location of FVs (salad bar, lunch line, or at the point of sale) and serving type (self-serve, pre-portioned) of each item on FV selection and consumption to inform best implementation practices.

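### The only stated use of baseline FV intake is a change score; adjusting for each school's baseline mean with an estimated slope would add about 7 points of power if the baseline–post correlation is 0.5, and nothing from about 0.8

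*Protocol article*

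**What the plan says.** Three places in the protocol article bear on how baseline enters the primary analysis.

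- **Design:** "The primary dependent variable of interest is change in FV intake, assessed using digital imagery plate waste methods". The hypotheses at the end of the Background are also worded as greater increases in salad-bar schools.
- **Design, text after Fig. 1:** "Inclusion of baseline assessments will allow us to control for any baseline differences between schools". It does not say how.
- **Analyses:** multilevel models compare Intervention and Control schools "at baseline and 4–6 weeks after salad bars are installed". "Potential covariates include grade, NSLP participation, and month of assessment, and factors related to the school cafeteria environment" that may differ between schools, where appropriate. The school's baseline FV intake is not named.

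The Power analysis assumes "J = 16 independent schools [8 Intervention and 8 Control", with "295 lunches per school", and contains no baseline term. Under Cafeteria procedures, numbered tray labels match a tray's before and after images and record grade and sex. Nothing described links a child's baseline lunch to the same child's later lunch.

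**The concern.** Without a child-level link, change can only be a difference between two school-level means. Under Target population and sample, the article expects 295 lunches per school per assessment date and 7,080 at each time point. Since 24 school-years × 295 = 7,080, each mean appears to rest on one rating day.

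A change score subtracts the baseline mean with a coefficient of exactly 1, however well or badly that day predicts the later one. If a school's intake varies materially between days or over time, the subtraction adds noise that an estimated slope would discount. With so few schools, precision depends on between-school variation. The baseline assessment is already paid for, and it is the plan's main means of reducing that variation.

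**Working it through.** **Inputs.** From the Power analysis: 16 schools split 8/8, n = 295, ICC 0.05 (also 0.01 and 0.10), minimum detectable effects 0.35 (0.17 and 0.48), α = 0.05. The Analyses section specifies two-sided tests. Rho, the baseline–post correlation of school means, is not in the document, so it is varied.

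**1. Reproduce the plan's figure.** Variance of a school mean = ICC + (1 − ICC)/n = 0.05 + 0.95/295 = 0.0532. SE of the arm difference = √(4 × 0.0532/16) = 0.1153. Minimum detectable effect = (t₀.₉₇₅,₁₄ + t₀.₈₀,₁₄) × SE = 0.348, matching 0.35. ICC 0.01 and 0.10 give 0.174 and 0.484, matching 0.17 and 0.48. Power at 0.35 is 80.5% (noncentral t, 14 df).

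**2. Variance factors, relative to post-only.**

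- Change score: 2(1 − rho), 14 df.
- Adjustment for the school baseline mean: (1 − rho²) × 13/12, 13 df. The 13/12 = 1 + 1/(16 − 4) is the expected cost of estimating the slope.

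**3. Worked case, rho = 0.5.** Change: factor 1.00, noncentrality 0.35/0.1153 = 3.04, power 80.5%. Adjusted: factor 0.75 × 13/12 = 0.8125, noncentrality 3.04/√0.8125 = 3.37, power 87.5%.

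**4. Across rho (ICC 0.05, effect 0.35; gaps from unrounded values).**

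| rho | Change | Adjusted | Gap (points) |
|---|---|---|---|
| 0.3 | 66.5% | 80.6% | 14.1 |
| 0.5 | 80.5% | 87.5% | 6.9 |
| 0.6 | 88.3% | 92.0% | 3.6 |
| 0.7 | 95.3% | 96.4% | 1.1 |
| 0.8 | 99.4% | 99.4% | under 0.1 |

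At rho 0.5 the gap is 7.3 points for ICC 0.01 and 7.1 for ICC 0.10. A simulation with 20,000 trials per cell at ICC 0.05 agrees: 66.0% against 80.5%, 80.5% against 87.6%, and 95.4% against 96.3% at rho 0.3, 0.5 and 0.7. Type I error was 4.8–5.1% for both methods.

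**5. Where change is as good.** The two factors are equal when 2 = (1 + rho) × 13/12, that is rho = 24/13 − 1 = 0.85. Above that, change has slightly the lower variance.

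**6. What would have to make rho moderate.** Lunch sampling contributes (0.95/295)/0.0532 = 6% of the school-mean variance at ICC 0.05. If that were the only source of discordance, rho would be 0.05/0.0532 = 0.94. A rho near 0.5 therefore needs real school-by-day or school-by-time variation.

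**7. Other layouts, rho = 0.5, ICC 0.05.** The Design section describes 12 pairs, in which eight schools serve first as Control and then as Intervention.

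- 24 school-years treated as independent (22 against 21 df, slope cost 1 + 1/20): 94.4% against 97.9%, a gap of 3.5 points.
- 12 pair differences with no credit for matching (11 against 10 df, slope cost 1 + 1/9): 92.2% against 95.5%, a gap of 3.3 points.

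**The case against.** **The article does not fix the estimator.** It names a variable of interest, promises control for baseline differences, and gives an open covariate list. A reader might infer that baseline is used only through change. The text does not go that far, and an unseen analysis plan could adjust for baseline. This stands as a limit on the wording. The point survives because the article does fix change as the primary variable and states no other mechanism.

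**Rho may be high.** Pairs are assessed concurrently, menus are matched where possible, and month is controlled. With 295 lunches, sampling noise is small. If rho is 0.8 or more there is nothing to gain. This stands as a limit on size. Against it, each mean appears to come from one day, menu matching is only where possible, and the Design section itself says that pupils are continually adjusting and that school breaks affect eating habits.

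**Adjustment relies on equal expected baselines.** From Year 2 the Intervention schools are the previous year's Controls, so arm is not freshly randomised in every pair, and a change contrast does not need that equality. This is a fair reason to keep the change contrast as a sensitivity analysis. It does not defeat the proposal, because schools are randomly selected within sociodemographic category.

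**The 8/8 calculation is not the actual layout.** This is correct. The 12-pair and 24-school-year versions roughly halve the gain at rho 0.5.

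**Conclusion.** The point holds as an avoidable inefficiency in the stated primary variable, worth correcting before analysis. On the plan's own power inputs the forgone power is about 14 points at rho 0.3, 7 at 0.5 and 1 at 0.7, with none from about 0.8. On the 12-pair or 24-school-year layout it is 3 to 4 points at rho 0.5. All of this rests on an assumed rho, so confidence in the size is moderate.

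Three stronger readings are not supported:

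- **That the trial loses 7 points against its stated 80%.** The power formula has no baseline term, and at rho 0.5 the change score has the same variance as that formula. Power falls below the stated figure only if rho is under 0.5.
- **That sampling noise in the baseline lunches is the cause.** It is about 6% of the school-mean variance at ICC 0.05.
- **That the change score is biased.** Given a chance baseline imbalance of one standard error (0.115 SD), the change estimate shifts by (1 − 0.5) × 0.115 = 0.058 SD at rho 0.5, about 16% of the 0.35 effect. This is conditional on the imbalance and averages out over randomisations. It is the same efficiency point seen from another side.

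**What to change.** State in the Analyses section that the primary contrast is post-launch FV intake, Intervention against Control, adjusted for that school-year's baseline mean FV intake as a school-level covariate with an estimated slope. Treat selection, dietary quality and energy in the same way, each with its own school baseline mean. Keep the difference-in-change contrast as a named sensitivity analysis, because the Year 2 and Year 3 Intervention schools are the previous year's Controls.

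The cost is a sentence or two fixed before analysis, with no new data. Statistically it costs one between-school degree of freedom, already counted in the power figures above, and reliance on equal expected baselines in the two arms, which the sensitivity analysis would help to check.
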